### Data analysis

No interim analyses to inform stopping guidelines will be required. The balanced characteristics between the intervention and control arms will be assessed by comparison of all baseline characteristics between the two study groups using χ^2^ test for dichotomous variables and either ANOVA or Kruskal-Wallis test for continuous data. Comparison of descriptive data will be made between participants who completed the study and those who dropped out to assess differential attrition. The primary and secondary outcomes (change over time in depression, anxiety, loneliness and social isolation) will be analysed using negative binomial and logistic regressions utilizing the Generalised Estimating Equations (GEE) approach, a marginal model in which the effect of covariates on the outcome is averaged over individuals at each point in time and is compared over time [38]. An exchangeable working matrix will be used to account for correlation and dependence between repeated measurements on the same individual over time while adjusting for study covariates.

Data analysis will investigate possible mediating variables explaining any relationship found between befriending and depression symptoms. Possible intervening variables of interest will include baseline depression/anxiety (higher is worse); baseline cognition (higher is better); and intensity of befriending (more befriending sessions are better). For the economic analysis, utility based outcomes, generated from application of the EQ-5D-5L, will be used to calculate the cost per quality-adjusted life-year (QALY) gained. Costs will include staff time spent preparing and producing training materials in addition to staff time spent administering/managing the befriending intervention. Unit costs for the mental health service utilization data will be derived from published fee schedules. Incremental cost effectiveness ratios and their associated confidence intervals will be estimated and cost effectiveness acceptability curves for varying threshold values of cost effectiveness will also be presented. An assessment of the sensitivity of the results obtained to variation in measured resource use, effectiveness and/or unit costs will be undertaken using appropriate one-way and multi-way sensitivity analysis.

A qualitative, phenomenologically based research design will be used to explore the experience of befriending from the perspective of the participants [39] and so to determine the acceptability and feasibility of the intervention. Colaizzi’s phenomenological data analysis steps will be used to describe the phenomena experienced by the participants and by the volunteers [40, 41].

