Befriending conversations can be delivered by volunteers. Research on the role of volunteers in health services has consistently shown positive effects for volunteers and older recipients of the service [21] including through: assisting with activities for socially isolated residents in aged care [22, 23]; engaging in social visits with residents in aged care [24]; and providing social support over the phone for people in the community with depression, anxiety and comorbid physical health problems [25]. When provided by volunteers, befriending has been found to significantly reduce depression symptoms in carers, those with a chronic illness, and the socially isolated, but again studies in RACF settings have not been published to date [26].

The primary aim of the BEFRIENDAS study is to test the effectiveness of befriending in relieving depression symptoms experienced by older adults living in RACFs compared with a control group receiving usual care. Secondary aims are to test its effectiveness in reducing symptoms of loneliness, anxiety, social isolation and improving quality of life. A conceptual framework or explanation for the mechanism underlying befriending is lacking in the literature, but we hypothesise that the impact of befriending on depression and anxiety is mediated by social support and reductions in loneliness (see Fig. 1).

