### Study design

The BEFRIENDAS study is an ongoing single blind pragmatic RCT comparing two groups of older people living in RACFs, one receiving weekly befriending for 4 months from a trained volunteer and the other receiving treatment as usual (TAU). As few previous RCTs of befriending have been conducted, TAU is an appropriate comparator. A clustered design is not necessary because the intervention is to be delivered at the individual level and not the RACF level. Furthermore, there is no evidence that RACFs have different policies on treatment of depression. Group allocation is blinded to the assessors but necessarily un-blinded to the participant. Participants undergo eligibility screening and assessments at three measurement time points: baseline prior to randomisation (T1), 2 months after the intervention starts (T2) and at the conclusion of the intervention 4 months post-baseline (T3). Figure 2 presents the flow of the participants through the study.

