### Randomisation

Following the baseline assessment, participants are randomly allocated to the befriending intervention group or the TAU control group. Relevant concomitant care and interventions such as psychological interventions or anti-depressants are noted and considered treatment as usual. Randomisation is managed by a trial statistician who is not directly involved in the study. A computer-generated random sequence available to the trial statistician, but no other research staff, is used to produce random allocation using a randomised permuted block design with block size of two in order to maintain approximately balanced randomisation throughout the trial. Randomisation is provided to an un-blinded researcher via email to verify that the correct allocation has taken place. The un-blinded researcher notifies the participants about their allocation and arranges for the intervention to begin. Research assistants conducting the assessments are blinded to group allocation.

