#### Assessment timepoints

Table 1 shows the timepoints when each outcome measure is conducted: at baseline assessment (T1), 2 months post commencement of intervention (T2) and follow-up assessment 4 months post commencement (T3).

**Table 1 Tab1:** Measures and assessment timepoints

Measure/Timepoint	Screen	T1 Baseline	T2 2 months post baseline	T3 4 months post baseline
GDS 15	✓		✓	✓
CSDD (from ACFI)^a^	✓			
PAS-CIS (from ACFI)^a^	✓			
GPCOG	✓			
Demographic data		✓		
GAI 20 item		✓	✓	✓
EQ-5D-5L		✓	✓	✓
UCLA Loneliness Scale		✓	✓	✓
Lubben Social Network Scale-6		✓		✓
Health service usage		✓		✓
Charlson comorbidity index		✓		✓
Medications		✓		✓
Satisfaction with befriending (qualitative data)				✓
Perceptions of befriending (qualitative data)				✓

^a^Provided to research team after resident provides consent to be involved in the study

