## Discussion

This study protocol presents the design of an ongoing RCT that aims to test the effectiveness of befriending by a volunteer on depression, anxiety and loneliness symptoms in older people living in residential aged care. To our knowledge, this is the first RCT evaluating the effectiveness of befriending on older people with depression living in residential aged care.

The introduction of the CSDD into the ACFI was a change in policy recognising the significance of psychological symptoms among RACF residents in Australia, but few other systematic efforts have addressed the issue. Guidelines around the management of depression, such as the NICE guidelines for the management of depression [11] are well established but not necessarily well implemented in RACFs where there is limited access to psychological services.

The befriending intervention, provided by trained volunteers over a four-month period, may reduce severity of depression experienced by older people living in RACFs, as well as the number of anxiety and loneliness symptoms. The results of this study will provide useful information about the effectiveness of a volunteer befriending program with older people living in RACFs, such as the necessary number of sessions required to have an impact on the resident, the length that the session needs to be and qualitative information on the acceptability of the delivery format, that is face-to-face or remotely via the telephone or video call.

If befriending, as conducted in this trial, proves effective, it is anticipated that befriending can be incorporated into health promotion programs such as the volunteer education program titled “Volunteers enriching older people’s wellbeing” offered by Beyond Blue, a health promotion organisation in Australia dedicated to improving mental health. It is also anticipated that this model may be adopted as a cost effective means of supporting residents with psychological symptoms living in RACFs. It is anticipated that it may be a complement rather than a substitute for other mental health support services. In light of the COVID-19 pandemic and the impact of lockdowns on the mental health of older people living in RACFs, the results of this study will be especially important to inform future models of care of the mental health of frail older people living in residential care [42, 43].

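### The mediation analysis names two pre-randomisation variables and a session count as possible mediators, and does not name the hypothesised mediators, loneliness and social support

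*Protocol article*

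**What the plan says.** The Background gives the mechanism as a hypothesis: "the impact of befriending on depression and anxiety is mediated by social support and reductions in loneliness". The caption of Fig. 1 confirms that a mediation model is meant.

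The Data analysis section takes up the subject: "Data analysis will investigate possible mediating variables explaining any relationship found between befriending and depression symptoms". Its next sentence gives the candidates: "Possible intervening variables of interest will include baseline depression/anxiety (higher is worse); baseline cognition (higher is better); and intensity of befriending". Intensity is defined there as the number of sessions, with more taken to be better. Loneliness and social support do not appear in this list.

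On timing, the Randomisation section states: "Following the baseline assessment, participants are randomly allocated to the befriending intervention group or the TAU control group". Table 1 places GDS-15 and GPCOG at screening and the anxiety scale first at T1. GPCOG is not repeated. The UCLA Loneliness Scale is taken at T1, T2 and T3, and the "Lubben Social Network Scale-6" at T1 and T3 only. Under Intervention, controls are offered a befriender only once their four-month assessment period is over, and those sessions are not evaluated.

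The Discussion expects the results to inform "the necessary number of sessions required to have an impact on the resident, the length that the session needs to be".

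**The concern.** A mediator must lie between allocation and outcome: allocation changes it, and the change carries through to the outcome. Two of the three listed items are fixed before allocation, so they fail the first condition. The third, session count, is close to a restatement of allocation when both arms are analysed together. When the intervention arm is analysed alone, it is an unrandomised exposure.

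If the list is followed as it stands, the analysis of the baseline items will report chance imbalance as if it were mechanism. The analysis of sessions may present a confounded association as a dose effect. The mechanism that the trial proposes would be tested only if someone adds it later, possibly after results are known. The Discussion foresees adoption in volunteer programmes, so a statement on how many sessions are needed could be taken up in practice.

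**Working it through.** The plan gives no figure to reproduce. The main argument is one of time order, and the numbers below only illustrate it.

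**1. Baseline depression/anxiety and baseline cognition.** All are measured at screening or T1, and allocation follows.
- Indirect effect = (effect of arm on mediator) × (effect of mediator on outcome, given arm).
- Randomisation makes the first factor zero in expectation, so the product is zero in expectation whatever befriending does.
- Illustration, with all effects assumed: 138 per arm (172 × 0.8 = 137.6); baseline variable b with SD 1; loneliness = 0.4b − 0.4·arm + noise (SD 1); depression = 0.5b + 0.4·loneliness − 0.11·arm + noise (SD 0.8). Over 2,000 simulated trials, the mean indirect effect through b was −0.0005 (SD 0.080).
- That SD is chance imbalance: √(2/138) = 0.120, times the coefficient of b, 0.5 + 0.4 × 0.4 = 0.66, gives 0.079.
- In the same trials the indirect effect through post-randomisation loneliness averaged −0.162 (SD 0.053), against the assumed −0.4 × 0.4 = −0.16.

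**2. Session count, both arms together.** Controls have 0 by design. Assume, for the intervention arm, a binomial count with 17 weekly opportunities and 75% attendance.
- Mean 17 × 0.75 = 12.75; variance 17 × 0.75 × 0.25 = 3.1875.
- With equal arms, between-arm variance = 12.75²/4 = 40.64 and within-arm variance averages 3.1875/2 = 1.594.
- r² with arm = 40.64/(40.64 + 1.594) = 0.962, so r = 0.98. Variance inflation = 42.23/1.594 = 26.5 (the simulation average was about 27).

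**3. Session count, intervention arm only.** Suppose frailty lowers attendance and raises GDS-15 at T3, and sessions have no effect at all. The spurious correlation is the product of the two paths; t = r√136/√(1 − r²) with n = 138.

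| Assumed paths | Spurious r | Two-sided p |
|---|---|---|
| −0.3 and +0.3 | −0.09 | 0.29 |
| −0.4 and +0.4 | −0.16 | 0.06 |
| −0.5 and +0.5 | −0.25 | 0.003 |

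The documents give neither correlation. The table shows a range without adjustment; it is not an estimate for this trial.

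**4. The list against the hypothesis.** Background: social support and loneliness. Data analysis: baseline depression/anxiety, baseline cognition, sessions. No item is common to both.

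**The case against.** The strongest reply is that the list is introduced as what the variables of interest will include, which leaves room for others. Loneliness and social isolation are analysed as outcomes in the same section, and UCLA loneliness is collected at all three time points. A condensed article may also leave the full mediation model to another document. This stands in part. A reader might infer that the plan rules out a test of its own mechanism; the documents do not say so, and the data permit the test. An open list still does not make a pre-randomisation value a mediator.

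Second, sessions follow allocation and lie on the path to the outcome. This also stands. A reader might infer that session count can never be a mediator, but that holds strictly only for the baseline items. For sessions the difficulty is near-collinearity with arm and lack of randomisation within the arm. The 0.98 depends on an assumed distribution, and counts do vary among intervention participants. The documents do not establish that frailty drives attendance: volunteer departures and COVID-19 restrictions may matter too. The Charlson index and the activities-of-daily-living measure are available for adjustment.

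Third, the Lubben schedule contradicts nothing. The protocol describes that scale as a measure of social isolation and nowhere designates it the social-support mediator, so its absence at T2 is not an error.

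Fourth, the Discussion sentence is an expectation, not an analysis commitment. That is fair, but it claims more than an unrandomised session count and length can show.

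**Conclusion.** The list is wrong as written and should be fixed. For baseline depression/anxiety and baseline cognition, the conclusion rests only on the protocol's own timing: the indirect effect is zero in expectation. For sessions, it rests on the zero count in controls and the absence of randomisation within the intervention arm; the size of the problem depends on assumptions, with illustrative spurious correlations from −0.09 (p = 0.29) to −0.25 (p = 0.003). Failure to name loneliness and social support is a mismatch with the Background, not an exclusion. Fig. 1 itself was not available, so this part rests on the Background sentence and the caption.

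A reader might infer that the trial's main result is at risk. It is not: mediation is a secondary explanatory analysis, and the primary comparison, the sample size and the randomisation do not depend on it.

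**What to change.** In Data analysis:
- Name UCLA loneliness at T2 as mediator of GDS-15 at T3, adjusted for baseline UCLA and baseline GDS-15 (the screening value in Table 1). State that T2 loneliness is itself not randomised, so the result assumes no unmeasured common cause of loneliness and depression.
- Treat the Lubben scale at T3, the nearest available measure of social support, as a concurrent exploratory analysis. Do not add a T2 assessment: the trial is ongoing, and participants already past T2 would have no value.
- Move baseline depression, anxiety and cognition to arm-by-baseline interaction (moderator) analyses.
- Report session number as an exploratory, non-causal dose or adherence analysis within the intervention arm, adjusted for baseline health measures already collected.

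A complier-average analysis for at least 12 sessions, with allocation as instrument, is best left out. It assumes that allocation does nothing for residents who receive 1 to 11 sessions, which nothing in the protocol supports. If it is used, that assumption must be stated.

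In the Discussion, say that the number and length of sessions will be described, and drop the claim that the trial will show what is necessary.

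The cost is a few sentences, with no new data and no change to the schedule. The change should be made before unblinded analysis, so that mediators are not chosen after results are seen.

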### Sample size

We are aiming for a clinically significant change of greater than two points in the GDS. Based on the average effect size of 0.27 for short term befriending outcome studies of mostly older adults with depression in primary care settings, it is estimated that with data collection spread over a three-year period, and allowing for a higher than usual dropout rate of 20% given low life expectancy among RACF residents, recruiting 172 participants per study arm (total of 344 participants) would achieve 80% power, with a statistical significance of 0.05. It is anticipated that each volunteer recruited may only befriend one participant, so a total of over 500 volunteers will be recruited throughout the study. Recruitment strategies to achieve the sample include wide ongoing advertisement and presentations in industry meetings and publications, monitoring quotas and widening locations where needed.

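### The planned confidence interval on the cost-effectiveness ratio may often be unbounded or uninterpretable if the QALY effect is modest; net monetary benefit with a CI would avoid this

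*Protocol article*

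**What the plan says.** The Data analysis section states that utilities from the EQ-5D-5L "will be used to calculate the cost per quality-adjusted life-year (QALY) gained". It then commits to a form of reporting: "Incremental cost effectiveness ratios and their associated confidence intervals will be estimated". The same sentence adds that "cost effectiveness acceptability curves for varying threshold values of cost effectiveness will also be presented", and the next says that an assessment of sensitivity "will be undertaken using appropriate one-way and multi-way sensitivity analysis". The method for the ratio interval is not named. Net monetary benefit and the cost-effectiveness plane are not mentioned.

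Table 1 schedules the EQ-5D-5L at T1, T2 and T3, so the horizon is 4 months. The Sample size section gives the only effect size and numbers available: "Based on the average effect size of 0.27 for short term befriending outcome studies of mostly older adults with depression in primary care settings", and "recruiting 172 participants per study arm (total of 344 participants) would achieve 80% power, with a statistical significance of 0.05", with 20% dropout. The 0.27 refers to befriending outcome studies in people with depression. No expected QALY difference, utility SD or cost difference appears anywhere.

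**The concern.** The incremental ratio divides the cost difference by the QALY difference. If the data cannot rule out a QALY difference of zero, they cannot rule out an arbitrarily large ratio of either sign.

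- A Fieller interval shows this openly: it becomes unbounded, either as two separate pieces or as the whole line.
- A bootstrap percentile interval hides it. It always gives two finite numbers, but the resamples behind them lie on both sides of zero QALYs. A negative ratio may then mean cheaper and better or dearer and worse. A positive ratio may mean dearer and better or cheaper and worse.

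Leaving the method unnamed does not remove the difficulty, because it lies in the quantity chosen. At stake is whether the interval the article promises can be read at all.

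**Working it through.** **The plan's own figures.** The plan states nothing about the precision of the ratio or of the QALY difference, so there is no figure to reproduce on this point. The sample size is used only as an input. (A two-sided unadjusted comparison at 0.27 SD needs 2 × (1.96 + 0.84)² / 0.27² ≈ 216 per arm, or 270 after 20% dropout, so 172 does not follow from it. That is a separate matter and does not affect what follows.)

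**Inputs.** Sample size section: 172 per arm and 20% dropout, giving 172 × 0.8 = 137.6 completers per arm. Table 1: EQ-5D-5L at 0, 2 and 4 months. Assumed, because the documents are silent: the standardised QALY effect d, the utility SD, and the correlation between visits.

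**When the interval is bounded.** Let ΔC and ΔQ be the cost and QALY differences. The 95% Fieller set holds every R with (ΔC − RΔQ)² ≤ 1.96² × [Var(ΔC) − 2R·Cov(ΔC, ΔQ) + R²·Var(ΔQ)]. The net coefficient of R² is ΔQ² − 1.96²·Var(ΔQ), so the set is bounded only if |ΔQ/SE(ΔQ)| > 1.96. When it is not bounded, more than Φ(−1.96) = 2.5% of approximately normal bootstrap resamples fall across zero QALYs from the estimate, which is the mixing of quadrants.

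**How often.** P(unbounded) = Φ(1.96 − m) − Φ(−1.96 − m), with m = d / √(2/n). For n = 137.6, √(2/n) = 0.1206. At d = 0.27, m = 2.24 and P = Φ(−0.28) ≈ 0.39.

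| True QALY effect (SD) | 137.6 per arm | 172 per arm (no dropout) |
|---|---|---|
| 0 | 95% | 95% |
| 0.10 | 87% | 85% |
| 0.20 | 62% | 54% |
| 0.27 | 39% | 29% |
| 0.34 | 20% | 12% |
| 0.50 | 1% | 0.4% |

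These are unadjusted. If adjustment for T1 utility had an assumed correlation of 0.6 with the outcome, d = 0.27 would act like 0.27 / √(1 − 0.36) ≈ 0.34, and the chance would fall from 39% to about 20%.

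**Same check on the utility scale.** By the trapezoid rule, QALYs = (u₁ + 2u₂ + u₃)/12. A utility gain g at T3, with g/2 at T2, gives ΔQ = (g + g)/12 = g/6. For utility SD s and a common correlation ρ between visits, the SD of QALYs is s√[(6 + 10ρ)/144] unadjusted and s√[(1 − ρ)(5 + 9ρ)/144] adjusted for T1. For example, with g = 0.05, s = 0.20 and ρ = 0.5, ΔQ = 0.0083 and the SE is 0.0067 unadjusted or 0.0044 adjusted. P(unbounded) is then 76% or 52%. Over assumed s of 0.15 to 0.30 and ρ of 0.5 to 0.7, adjusted or not:

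| Assumed gain at T3 | ΔQ | P(unbounded) |
|---|---|---|
| 0.02 | 0.0033 | 78–94% |
| 0.03 | 0.0050 | 56–93% |
| 0.05 | 0.0083 | 15–88% |
| 0.08 | 0.0133 | 0–77% |

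**The case against.** The strongest reply is that this is a general caution about any cost-effectiveness ratio and that the plan already holds the usual safeguard. At each threshold an acceptability curve gives the probability that net benefit is positive, and it stays defined when the QALY difference is near zero. This largely stands: the decision need not rest on the ratio interval. It does not dispose of the point, because the curves are presented in addition to the interval, which would still be reported.

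A second reply is that the interval method is a detail an article may leave to the full analysis plan. That is true, and its absence is no finding. The article does, however, fix the quantity to be given an interval, and any method must deal with a denominator that may straddle zero.

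Three stronger readings are tempting and are not supported:

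- A reader might infer that the interval would lose its 95% coverage. An unbounded Fieller set keeps its coverage, and it reports correctly that the data do not pin down the ratio. No shortfall is shown here for any other method, and none is chosen in the plan.
- A reader might infer that the QALY difference is probably near zero because follow-up is only 4 months. The documents give no QALY effect or SD. A small absolute figure such as 0.005 QALY settles nothing either, since expressing a given utility pattern in years scales the effect and its SE alike. At 0.27 SD a bounded interval is the likelier result (61%).
- A reader might infer that a stated trial aim is undermined. The aims at the end of the Background are depression, loneliness, anxiety, social isolation and quality of life. Cost-effectiveness is the purpose of the accompanying economic evaluation and is not listed among them.

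**Conclusion.** The point holds as a modest, low-cost improvement to the analysis. The article commits to an interval on a ratio that will often be unbounded or hard to interpret if the QALY effect is modest: about 39% of the time at 0.27 SD, 62% at 0.20 SD and 87% at 0.10 SD, but only about 1% at 0.50 SD. These figures assume 137.6 completers per arm, an approximately normal QALY difference and no baseline adjustment, which would lower them. Carrying the depression effect over to QALYs is an assumption and not something the plan claims. On the utility scale the result runs from 0% to 94% over the inputs tried, so the size depends on figures the documents do not give. What is lost is a readable statement of uncertainty about the ratio; the planned acceptability curves contain the damage to the decision itself.

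**What to change.** Revise the sentence in the Data analysis section so that the economic results are:

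- incremental costs and incremental QALYs, each with a 95% CI;
- the cost-effectiveness plane;
- incremental net monetary benefit, λΔQ − ΔC, with its 95% CI over the same threshold values λ as the acceptability curves;
- the acceptability curves, as already planned;
- the incremental cost-effectiveness ratio as a point estimate, with an interval only when the QALY difference is clearly away from zero (for instance, when its own 95% CI excludes zero).

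Net benefit is linear in costs and QALYs. Its variance, λ²Var(ΔQ) + Var(ΔC) − 2λCov(ΔC, ΔQ), is finite whatever the size of ΔQ, so its interval can be read at every threshold.

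No new data are needed. The cost is slightly more reporting, and net benefit has to be read against stated thresholds where a ratio does not.
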